### Withdrawal and safety

Due to the nature of this cluster trial which uses a waiver of consent and data collection from routine sources, a typical trial withdrawal process is not appropriate. However, information about the study is available at NHS sites (posters, leaflets) and patients whose data may be included can request more information and removal of data should they wish.

Similarly, due to the nature of the trial, a standard safety monitoring and reporting system is not appropriate. As described above, there should be minimal risk to people who receive any part of the study intervention which aims to facilitate access to an existing evidence-based treatment. However, data collected for the study include care processes indicators (eg, time to hospital arrival and time to receipt of intravenous thrombolysis) and health outcomes which are intermittently reviewed unblinded to randomisation group by a study Data Monitoring Committee (Safety Committee).

### Outcomes

#### Primary outcome

This study has a co-primary outcome of:

thrombectomy rate.the time from stroke symptom onset to thrombectomy (when thrombectomy is received).

The primary analysis will be conducted using the primary analysis population (see also Study population’, above).

If the stroke symptom onset time is unclear, the ‘last known well’ time will act as the onset time in keeping with standard clinical practice.

Time of thrombectomy will be defined by the time of arterial puncture whether or not thrombus is subsequently removed.

#### Secondary outcomes

Thrombectomy treatment rate and time to treatment (using other analysis populations).Key ambulance time intervals using the following data: emergency call, ambulance dispatch, arrival on scene, leave scene, arrival at first hospital.Key hospital time intervals using the following data: stroke symptom onset, hospital arrival, brain imaging, thrombolysis (when thrombolysis is received).Thrombolysis rate.Radiological success in re-canalising the arterial occlusion (assessed by modified TICI score).^31^Stroke severity (National Institute for Health Stroke Scale (NIHSS)^32^ at 24 hours post reperfusion treatment.Total length of hospital stay (stroke patients only).Dependency at discharge (Modified Rankin Scale (mRS)^33^ including death) from total hospital stay (stroke patients only).CSC admission and transfer rates.Length of stay at a CSC (stroke patients only).

### Sample size

The study is powered using the primary analysis population (as defined above in ‘Study population’). The primary analysis population was chosen because it is the group where direct effects of the intervention can be most appropriately assessed, ie, the population eligible for both pathway deployment and subsequent thrombectomy treatment.

Considering the primary analysis population, the study is powered to detect a clinically meaningful reduction of 30 minutes in the time from stroke onset to thrombectomy and to demonstrate whether there is a change to the thrombectomy treatment rate.

Time to treatment: For 90% power (one-sided 5% significance level) to conclude that the intervention reduces the time from onset to treatment, data from *564* participants are required. This calculation assumes a random effect for clusters (ambulance stations), 1:1 allocation of 150 clusters to the two groups, and an intracluster correlation of 0.01 (based on previous similar ambulance trials which demonstrated minimal clustering).^34 35^ The standard deviation of the onset to treatment time is taken as 120 minutes, based upon available national audit data.^11^

Treatment rate: Assuming a conservative baseline thrombectomy rate of 3% in the total stroke population across centres, an important absolute change in procedures would be 2% (ie, a decrease to 1% or increase to 5%), which is equivalent to a change of 8.4% amongst the primary analysis population (baseline 13.2%, decrease to 4.8% or increase to 21.6%). To confirm whether the intervention changes treatment rates compared with standard care, *894* participants are required to detect an 8.4% difference (using change from 13.2% to 21.6% which gives the higher sample size, two-sided 5% significance level; power 90%; ICC 0.01 for 150 clusters with 1:1 randomisation).

The total size of the primary analysis population, however, will be dependent on CSC thrombectomy rates as this will determine the availability of patients for the time to treatment analysis. Based on previously published work,^11 21^ the investigator team have estimated that the primary analysis population size will be between 2600 and 4300 patients if thrombectomy services are running at 5% and 3% of all stroke patients, respectively.

The total size of the full study population is dependent on the rate at which suspected/stroke patients present to services, and the size and opening order of regions taking part in the trial. Estimations using historical data suggest that the full study population will be approximately 80 000 patients.

Because the data required for the time to thrombectomy treatment analysis are mandatory national audit fields, the sample size estimate has not been inflated for attrition. However, availability of these data will be regularly monitored and trial enrolment will not cease until appropriate data are available for 564 relevant thrombectomy treated patients. As described above, to achieve this number of thrombectomy treatments, the sample size estimate for treatment rate should be easily exceeded and will therefore allow for any potential attrition in receipt of thrombectomy information.

### Study timeline

Trial enrolment commenced in the first participating region on 7 November 2022. Enrolment will end when time to thrombectomy treatment data are available for the required 564 patients from the primary analysis population. At submission of this manuscript, five NHS ambulance services which routinely convey patients to 26 PSCs and eight CSCs are involved in the study. The eight CSCs receive SPEEDY pathway calls from regional ambulance practitioners randomised to the intervention group. Accruing study data are regularly monitored and relevant time to thrombectomy treatment information for 564 participants in the primary analysis population is expected to be obtained by December 2025. First study results are expected in summer 2026.

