#### Primary analysis

The primary analysis will use the primary analysis population with the estimands framework strategy^36^ applied to intercurrent events to define the analysis groups. The intercurrent events of importance and the chosen estimands strategies are shown in table 2.

**Table 2 T2:** Intercurrent events of importance in the SPEEDY trial

Intervention group		Control group	
Intercurrent event	Strategy	Intercurrent event	Strategy
1. SPEEDY pathway not initiated or telephone call not answered.	Principal stratum	1. SPEEDY pathway initiated and call answered	Principal stratum
2. No conveyance decision made during SPEEDY pathway call (eg, call abandoned) or decision is conveyance to local PSC due to capacity limitations at the CSC.	Treatment policy		

CSC, comprehensive stroke centre; PSC, primary stroke centre; SPEEDY, Specialist PrE-hospital rEDirection for ischaemic stroke thrombectomY.

*Intervention primary analysis group*: this comprises only patients where the SPEEDY pathway was initiated/contact with the CSC was made. Patients where the attending intervention group assigned ambulance practitioner fails to initiate the pathway or cannot establish contact with the CSC will not feature in this analysis group. However, where the pathway is initiated and contact with the CSC is achieved, patients will remain in the group regardless of the conveyance decision made (ie, whether they are redirected to the CSC or sent to the local PSC) and whatever treatment decision is made (ie, whether they receive a thrombectomy or not via either route).

This approach to defining the intervention primary analysis group is being taken because it reflects the impact of the SPEEDY pathway when it is used during patient care and separates this from the additional impact of ambulance service deployment rate. As a cluster trial (chosen to minimise contamination), if a classic intention to treat (ITT) approach is employed, the group primary outcome data (thrombectomy rate and time from onset to treatment) become influenced by ambulance service deployment rates of a research intervention, ie, because the intervention group in this cluster trial comprises any patient attended by an intervention assigned ambulance practitioner, the group would contain both patients who had received the pathway and those where the attending practitioner had not deployed it.

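### Enrolment stops at 564 thrombectomies in the whole primary analysis population, but the primary analysis drops intervention patients without pathway contact, so the stated 90% power for time to treatment is not assured

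*Protocol article*

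**What the plan says.** The Sample size section states that the trial is "powered to detect a clinically meaningful reduction of 30 minutes in the time from stroke onset to thrombectomy". The calculation is set out as "For 90% power (one-sided 5% significance level) to conclude that the intervention reduces the time from onset to treatment", with 150 clusters allocated 1:1, an intracluster correlation of 0.01 and a standard deviation of 120 minutes. The result is 564 participants, not inflated for attrition because the time fields are mandatory in the national audit.

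The stopping rule appears twice. The Sample size section says "trial enrolment will not cease until appropriate data are available for 564 relevant thrombectomy treated patients". The Study timeline section says "Enrolment will end when time to thrombectomy treatment data are available for the required 564 patients from the primary analysis population", and repeats the same population when it gives the expected completion date. The Sample size section also forecasts that "the primary analysis population size will be between 2600 and 4300 patients".

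The Study population section defines the primary analysis population by clinical criteria, time window, location and a hospital diagnosis of ischaemic stroke. Use of the pathway is not a condition.

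The Primary analysis section then applies a principal stratum strategy. An intervention patient whose practitioner "fails to initiate the pathway or cannot establish contact with the CSC will not feature in this analysis group". Control patients for whom the pathway was used are also removed, but these are expected to be few.

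**The concern.** The number that gives 90% power and the number that ends enrolment are counted over different sets of patients. The section headed Other information about the pathway says that intervention patients for whom the pathway was not deployed may still have thrombectomy after secondary transfer. Each of them moves the trial one step closer to stopping but adds nothing to the primary comparison. The analysed intervention arm ends up smaller than planned.

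The protocol itself expects this. The Primary analysis section calls the deployment rate unpredictable, says a practitioner meets a qualifying patient only every 4 to 6 months, and gives non-deployment as the reason for the chosen estimand. The sample size makes no allowance for it. The reason given for not inflating (mandatory audit fields) covers missing data, not planned exclusion.

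The time test is the gatekeeper: if it fails, the rate hypothesis is not tested and the pathway cannot be declared effective. The rate co-primary has ample power of its own (about 99% or more at 50% deployment with 2600 to 4300 patients), but that reserve cannot be used if the time test fails.

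**Working it through.** **Inputs from the Sample size section:** effect 30 minutes; SD 120 minutes; one-sided 5%; power 90%; ICC 0.01; 150 clusters, 75 per arm; thrombectomy rates 13.2% and 21.6%.

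**Assumed, because the protocol gives no value:** the deployment rate d, meaning the share of eligible intervention patients with pathway initiation and CSC contact. A range is shown. Control exclusions are taken as nil.

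**1. Reproduce 564.**
- Unclustered total: 4 × (120/30)² × (1.645 + 1.282)² = 548.1.
- Design effect: 1 + (564/150 − 1) × 0.01 = 1.0276.
- Product: 548.1 × 1.0276 = 563.2, hence 564.
- At 282 per arm the power is 90.0%. So 564 is the number that must be inside the comparison.

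**2. Reproduce the forecast.** 564/0.216 = 2611 and 564/0.132 = 4273, which match the stated 2600 and 4300. All 564 are spread over the whole population, with nothing added for exclusions.

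**3. Power with the trigger as written.** With n_c control and n_t intervention procedures analysed:
- SE = 120 × √(DE_c/n_c + DE_t/n_t), where DE = 1 + (n/75 − 1) × 0.01 in each arm
- Power = Φ(30/SE − 1.645)

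*Scenario A, equal thrombectomy rates.* Then n_c = 282 and n_t = 282d. Example at d = 50%: n_t = 141, DE_c = 1.0276, DE_t = 1.0088, SE = 12.47, power = Φ(2.406 − 1.645) = 77.7%.

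*Scenario B, 21.6% treated among contacted patients and 13.2% in everyone else.* Enrolment stops when the three sources of procedures total 564, so patients per arm = 564/[0.132 + 0.216d + 0.132(1 − d)]. At d = 50% this is 1843 per arm: 243 control procedures, 199 contacted and 122 excluded. SE = 11.58, power = 82.8%.

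| Deployment d | A: control v intervention analysed | A: power | B: control v intervention analysed | B: power |
|---|---|---|---|---|
| 100% | 282 v 282 | 90.0% | 214 v 350 | 88.5% |
| 80% | 282 v 226 | 86.9% | 225 v 294 | 87.4% |
| 70% | 282 v 197 | 84.6% | 231 v 264 | 86.4% |
| 50% | 282 v 141 | 77.7% | 243 v 199 | 82.8% |
| 30% | 282 v 85 | 64.2% | 257 v 126 | 74.0% |

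In A, power at d = 87% is 88.2%, so the loss is under 2 points above about that rate. In B, power is already 88.5% at full deployment because the arms are unequal; that 1.5-point shortfall has nothing to do with the exclusions.

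**4. Size under a corrected trigger (scenario A, d = 50%).** Only 1.5 of every 2 procedures are analysed, so 564 analysed means 564/0.75 = 752 in the whole population. The forecast becomes 752/0.216 = 3481 to 752/0.132 = 5697, or about 3500 to 5700. The split is then 376 v 188 and power is about 87%. Restoring a full 90% takes about 846 procedures in the whole population (423 v 211.5 analysed).

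**The case against.** **The actual power is unknown.** This stands. A reader might infer that the trial is shown to be underpowered, or that its power is one of the lower figures above. The documents do not support that. They state no deployment rate, and with high deployment the loss is trivial. What they do show is that the 90% depends on a condition that the protocol neither states nor expects to meet.

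**Equal thrombectomy rates are pessimistic.** This also stands. The protocol's own planning effect on rate puts more procedures in the contacted group and softens the loss, which is why both scenarios are shown. The loss does not disappear: power is 83% at 50% deployment and 74% at 30%.

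**The true effect among contacted patients may exceed 30 minutes.** It may. At 50% deployment with equal rates, about 36.5 minutes would restore 90%. But the protocol fixes 30 minutes as the effect to detect and does not make this argument.

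**The wording may already mean analysed patients.** The Sample size section speaks of relevant treated patients, and that word is undefined. The Study timeline section names the primary analysis population twice, and its definition does not depend on pathway use. If analysed patients are meant, the wording and the forecast still need correcting.

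**The statistical analysis plan will settle it.** The protocol defers the analyses and populations to that plan, but it fixes the sample size and the stopping rule itself, and those are what fail to match.

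**The secondary intention-to-treat analysis.** A reader might add that it loses power too. The protocol claims no power for it, so no stated figure is wrong there.

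**Conclusion.** The point holds as a mismatch between the stopping rule and the primary analysis set. The 564 itself is correct for its stated inputs; it is applied to the wrong count of patients. The stated 90% power for the gatekeeping time test is not assured and falls with any material non-deployment. Over assumed deployment from 80% down to 30%, power runs from about 87% to 64% with equal thrombectomy rates, and from about 87% to 74% under the protocol's 13.2% and 21.6%. These figures rest on a 30-minute effect in the analysed groups, SD 120 minutes, ICC 0.01, one-sided 5%, negligible control exclusions, and a deployment rate that the documents do not give. They concern power only, not any selection effect of the exclusion.

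**What to change.** Choose one of two and say so in both the Sample size and Study timeline sections.

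1. Define the trigger as 564 procedures in patients who enter the two estimand-defined primary analysis groups, and revise the 2600 to 4300 forecast to match. At 50% deployment with equal rates it becomes about 3500 to 5700. State the expected arm split too, since an uneven split still costs something (about 87% power in that case).
2. Keep the trigger over the whole population, say so plainly, and replace the 90% with the power at the assumed or observed deployment rate and arm split.

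Power for the intention-to-treat analysis could be added but is optional.

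The second option costs wording and a less favourable power figure. The first may also extend enrolment. Either needs a deployment rate. The call log gives only the numerator, because it records calls that were made; the denominator of eligible intervention patients needs the linked ambulance and SSNAP data that the trial already collects.

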### Statistical analyses

All analyses and analysis populations will be fully described in a detailed statistical analysis plan.

#### Primary analysis

The primary analysis will use the primary analysis population with the estimands framework strategy^36^ applied to intercurrent events to define the analysis groups. The intercurrent events of importance and the chosen estimands strategies are shown in table 2.

**Table 2 T2:** Intercurrent events of importance in the SPEEDY trial

Intervention group		Control group	
Intercurrent event	Strategy	Intercurrent event	Strategy
1. SPEEDY pathway not initiated or telephone call not answered.	Principal stratum	1. SPEEDY pathway initiated and call answered	Principal stratum
2. No conveyance decision made during SPEEDY pathway call (eg, call abandoned) or decision is conveyance to local PSC due to capacity limitations at the CSC.	Treatment policy		

CSC, comprehensive stroke centre; PSC, primary stroke centre; SPEEDY, Specialist PrE-hospital rEDirection for ischaemic stroke thrombectomY.

*Intervention primary analysis group*: this comprises only patients where the SPEEDY pathway was initiated/contact with the CSC was made. Patients where the attending intervention group assigned ambulance practitioner fails to initiate the pathway or cannot establish contact with the CSC will not feature in this analysis group. However, where the pathway is initiated and contact with the CSC is achieved, patients will remain in the group regardless of the conveyance decision made (ie, whether they are redirected to the CSC or sent to the local PSC) and whatever treatment decision is made (ie, whether they receive a thrombectomy or not via either route).

This approach to defining the intervention primary analysis group is being taken because it reflects the impact of the SPEEDY pathway when it is used during patient care and separates this from the additional impact of ambulance service deployment rate. As a cluster trial (chosen to minimise contamination), if a classic intention to treat (ITT) approach is employed, the group primary outcome data (thrombectomy rate and time from onset to treatment) become influenced by ambulance service deployment rates of a research intervention, ie, because the intervention group in this cluster trial comprises any patient attended by an intervention assigned ambulance practitioner, the group would contain both patients who had received the pathway and those where the attending practitioner had not deployed it.

As a research project, it is not possible to take advantage of systems used to enforce clinically adopted pathways across a large dispersed ambulance workforce such as mandatory audit, staff training and regular feedback. Instead, research relies on softer approaches for engagement such as regular communication and attempting to maintain a positive research culture. Ambulance assessed patients meeting the pathway criteria do not occur frequently for individual practitioners. It is estimated that an average of 1–2 suspected stroke patients per month are assessed by an individual practitioner, but only every 4–6 months will one of these patients fulfil the pathway initiation criteria. Therefore, individual practitioners are required to recognise an infrequent event under time pressure in the uncontrolled prehospital environment, and then remember to deploy a research intervention.

Using this described estimands intercurrent events strategy to define the intervention primary analysis group allows the impact of the pathway to be assessed without influence of an unpredictable deployment rate. This approach also makes the results more generalisable to any healthcare setting (inside and outside the UK) where any future deployment (implementation) rate may differ for different reasons.

*Control primary analysis group*: this comprises only patients where the SPEEDY pathway was NOT initiated. Any patients where the SPEEDY pathway was used will be excluded. This scenario, however, where the pathway is initiated by control assigned staff (in error), should be infrequent due to the cluster design.

*Analysis*: using the estimands defined groups, the co-primary outcomes of thrombectomy rate and time to thrombectomy will be examined using a two-part regression model. The model will be adjusted for predefined baseline covariates and the stratification variables of size of ambulance station and distance from a CSC.

Part 1 of the model will determine the chance of thrombectomy treatment occurring as a binary variable. Part 2 of the model will then analyse time to treatment as a continuous variable, conditional on thrombectomy having occurred.

Hypothesis testing for the co-primary outcomes will use a fixed-sequence procedure to account for multiple testing.^37^ The hypothesis for time from symptom onset to thrombectomy will be tested first at a 5% significance level. Only if the null hypothesis for time to treatment is rejected will the hypothesis for thrombectomy rate be tested, also at a 5% significance level. This sequence (ie, time before rate) is chosen because the effect of the trial intervention (SPEEDY pathway) on time to treatment is more important clinically than an effect on rate.

To conclude that the SPEEDY pathway is effective, a statistically significant difference between the groups is required for time to thrombectomy, *or*, both time to thrombectomy and thrombectomy rate.

As described above in ‘Sample size’, there should be no missing data for the co-primary outcomes and therefore an imputation strategy should not be required.

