#### Secondary analyses

Using the primary analysis population, a standard ITT approach will be applied to examine the rate and speed of thrombectomy treatment.

Secondary outcomes will be evaluated using both the primary and other analysis populations. According to the type of data, linear or generalised linear models will be used. Both unadjusted analyses and analyses which adjust for predefined baseline covariates and the stratification variables will be undertaken. Analyses will be on a complete case basis, although if required, additional sensitivity analyses will be undertaken using an appropriate imputation method.

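### The primary analysis labelled principal stratum compares intervention patients who got the pathway with nearly all controls, so selection can create or hide an effect

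*Protocol article*

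**What the plan says.** All references are to the protocol article.

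- **Intervention group** (Primary analysis): "this comprises only patients where the SPEEDY pathway was initiated/contact with the CSC was made". A patient whose intervention practitioner "fails to initiate the pathway or cannot establish contact with the CSC will not feature in this analysis group". Once contact is made, patients stay in whatever the conveyance or treatment decision.
- **Control group** (Primary analysis): "this comprises only patients where the SPEEDY pathway was NOT initiated". The only exclusion is the case "where the pathway is initiated by control assigned staff (in error), should be infrequent due to the cluster design".
- **Label** (Table 2): "SPEEDY pathway not initiated or telephone call not answered" is handled by a principal stratum strategy in the intervention arm. Erroneous initiation carries the same label in the control arm.
- **Model** (Primary analysis): a two-part regression adjusted for predefined baseline covariates, station size and distance from the CSC.
- **Testing** (Primary analysis): time to thrombectomy is tested first at 5%, and rate only if time is rejected. A significant time result is enough to declare the pathway effective.
- **Intention to treat** (Secondary analyses): in the same population, "a standard ITT approach will be applied to examine the rate and speed of thrombectomy treatment".

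**The concern.** The stratum the authors want is patients in whom the pathway would be initiated and answered if an intervention practitioner attended. Randomisation puts such patients in both arms, but among controls they cannot be seen. The plan selects them in the intervention arm by an event after randomisation. It does nothing to find, weight or model their counterparts among controls. The control group is therefore a mixture of would-be-used and would-not-be-used patients.

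The two sides are comparable only if use is unrelated to outcome given the covariates. The article does not claim that. It says that "individual practitioners are required to recognise an infrequent event under time pressure in the uncontrolled prehospital environment", and cases that are easier to recognise may plausibly differ in their chance and timing of thrombectomy. The Blinding section defends the open design on the ground that staff cannot choose who enters the trial. Under the primary analysis, however, the practitioner's decision to call, and whether the call is answered, decides who enters the headline comparison.

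At stake is the trial's conclusion, because effectiveness is declared from these tests and the randomised comparison is only secondary.

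**Working it through.** **1. The plan's own figures reproduce.** Inputs from Sample size: 30 minutes, SD 120, one-sided 5%, 90% power, ICC 0.01, 150 clusters.

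- Time: 2 × (1.645 + 1.282)² × (120/30)² ≈ 274.04, rounded up to 275 per arm, 550 in total. With design effect 1 + (N/150 − 1) × 0.01, N = 550 × 0.99 / (1 − 550/15000) ≈ 565. The article states 564, and power at 564 is 90.0%.
- Rate: 13.2% v 21.6%, two-sided 5%, gives 426 per arm, 852 in total. Then 852 × 0.99 / (1 − 852/15000) ≈ 894, as stated.

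The problem is therefore not an arithmetic error in the sample size.

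**2. Bias in the time contrast when the pathway does nothing.** Let c be the share of treated intervention patients in whom the pathway was used, and d the mean difference in time, used minus non-used. With no effect, both arms have mean c·μ(used) + (1 − c)·μ(non-used). Hence

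E[used] − E[all controls] = (1 − c) × d.

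This is zero only if c = 1 or d = 0 (given the covariates).

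**3. False rejection of the time hypothesis.** The article gives neither c nor d, so both are assumed. Take 282 treated controls and 282c treated used patients, with no covariate adjustment:

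SE = 120 × √[(1/282 + 1/(282c)) × (1 + ((282 + 282c)/150 − 1) × 0.01)].

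At c = 0.5, SE = 12.49 and the bias is 0.5 × 30 = 15 minutes, so z = 1.20. The one-sided rejection probability is Φ(1.20 − 1.645) = 0.33. The Primary analysis section does not say whether the test is one- or two-sided, so both are shown.

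| c | d (min) | bias (min) | one-sided 5% | two-sided 5% |
|---|---|---|---|---|
| 0.3 | −30 | −21 | 40% | 29% |
| 0.5 | −30 | −15 | 33% | 22% |
| 0.7 | −30 | −9 | 20% | 13% |
| 0.9 | −30 | −3 | 9% | 6% |
| 0.5 | −60 | −30 | 78% | 67% |
| any | 0 | 0 | 5% | 5% |

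Simulation (4000 trials per case) gave 32.9% and 22.6% for c = 0.5, d = −30. Intention to treat on the simulated trials stayed between 4.5% and 5.4%, tested one-sided. With d positive the bias changes sign and a real benefit is hidden.

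**4. Bias in the rate estimate.** Assume 50% deployment, an overall rate of 13.2% in both arms, and used patients 1.5 times as likely to be treated as the rest. The non-used rate is 0.132 / (0.5 × 1.5 + 0.5) = 10.6%, and the used rate is 1.5 times that, 15.8%. The planned contrast then shows 15.8% v 13.2%, a spurious 2.6 points. In a simulation with a true difference of 8.4 points it estimated 11.0, while intention to treat divided by uptake recovered 8.4.

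**The case against.** The authors' choice is disclosed and argued. They want the effect of the pathway when it is used, separate from a deployment rate that a research project cannot enforce. That is a legitimate question, and intention to treat is prespecified beside it. Both arms are already restricted to arm weakness plus speech disturbance, the 5-hour limit, the operating window, a PSC catchment area and confirmed ischaemic stroke. This removes some of the variation in how recognisable a case is. The reasons given for non-deployment (rarity, time pressure, remembering a research task) are partly practitioner factors, and where these are unrelated to outcome they add no bias. The covariates are left to an analysis plan that is not shown.

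This stands as a reason to treat the size of the bias as unknown. It does not repair the comparison: the article fixes the groups and the type of model, and nothing in it identifies the stratum among controls.

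Three stronger readings are tempting and are not supported.

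- **That the rate test has its own large trial-level error.** Taken alone, the example in step 4 would reject in about 45% of trials at 4300 patients. But rate is tested only after time is rejected, so the example shows a biased estimate, not a stand-alone trial error rate.
- **That the bias favours the pathway.** Nothing in the article fixes its sign.
- **That dropping unanswered calls contradicts the rationale.** One might say that a call the CSC misses is a pathway failure, not a deployment failure. But the article also aims at the pathway's effect when actually used. Without contact there is no remote assessment, and crews are advised to revert to standard care. How to treat that event is a choice of estimand.

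**Conclusion.** The point holds. The planned primary comparison is a per-protocol contrast under a principal stratum label. It is unbiased only if deployment is complete, or if initiation and call answering are unrelated to outcome given the model's covariates. The secondary intention-to-treat analysis does not rescue it, because the conclusion of effectiveness follows the primary tests.

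The size is conditional. Under the assumed 50% deployment and 30-minute difference, the bias is 15 minutes against a 30-minute target, with about 33% (one-sided) or 22% (two-sided) false rejection of the first-tested hypothesis. At 90% deployment this falls to about 9% or 6%. These figures are unadjusted, and good covariates could reduce them. A reader might infer that the trial's type I error is known to be inflated. The documents show only that it is not protected, and that a benefit could be either created or hidden.

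**What to change.** 1. Make the already planned intention-to-treat comparison in the primary analysis population the confirmatory, randomised test of both outcomes, in the existing order.
2. Keep the estimand for patients in whom the pathway would be used, and estimate it with methods suited to that stratum:
   - *Rate:* complier average causal effect, that is, the intention-to-treat difference divided by the between-arm difference in pathway use. Allocation is the instrument and standard errors are clustered by station.
   - *Time:* weight controls by their predicted probability of initiation, from a model fitted in the intervention arm (principal-score weighting). State the assumptions: initiation is ignorable given the covariates, and the outcome is defined only in treated patients. Add a sensitivity analysis. The ignorability assumption is untestable, so this must not be presented as restoring randomisation.
3. Leave the handling of unanswered calls as the authors' choice of estimand.

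**Cost.** This is analysis work and wording, to be agreed before unblinded analysis.

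Intervals widen. For rate at 50% deployment and 4300 patients, ignoring clustering, the SE is √(0.132 × 0.868 × 2/2150) / 0.5 = 2.1 points. For the planned contrast it is √(0.132 × 0.868 × (1/2150 + 1/1075)) = 1.3 points.

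The intention-to-treat effect is diluted. If the true effect is 30 minutes in used patients and zero in the rest, 50% deployment leaves 15 minutes. With 282 treated per arm the SE is 10.24, so one-sided power is Φ(15/10.24 − 1.645) ≈ 43%. At 90% deployment (27 minutes) it is about 84%. The sponsor should weigh this openly against the stopping target of 564 treated patients.
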